### Statistical analysis plan

A sample size of 300 patients was initially anticipated. As the epidemic in Sao Paulo grew fast, the hospital included new ICU beds, and we revised the anticipated sample size to 500 patients. Given that the study carries no risks for participants and that the requirement for informed consent was waived by the IRB, we intend to collect data on all patients with COVID-19 admitted to the ICUs during the study period, a sample possibly larger than the anticipated sample size. Such a large sample would suffice to allow identification of predictors of survival.

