Categorical variables will be expressed as counts and percentages, and continuous variables, as mean (standard deviation) or median (interquartile range), as appropriate. All hypothesis tests will be two-tailed, with a significance level of 0.05, and they will be performed using the R software (R Core Team, 2016, Vienna, Austria). We will build Kaplan-Meier curves to estimate 28-days survival. ICU survival will be defined as the time interval between ICU admission and patient death from any cause or ICU discharge. Time will be censored at 28 days for patients who are still alive. Hospital survival will be defined as the time interval between ICU admission and patient death from any cause or hospital discharge. Patients discharged home will be considered alive at day 28. We will perform survival analysis using the Cox proportional hazards model censored at 28 days to identify the main risk factors for ICU survival beyond expected associations, such as age, comorbidity burden, and severity of disease at ICU admission. Variables identified *a priori* as clinically relevant (Table 5) and additional variables with a *p*-value <0.20 in a univariate analysis will be evaluated as independent risk factors of poor prognosis in a multivariable Cox model. The order of inclusion of variables into Cox multivariable models will follow statistical significance criteria and clinical relevance. Alternative models will be chosen on the basis of information criteria and likelihood ratio-based tests. Wherever possible, continuous variables will be modeled to account for nonlinearity with splines or polynomials and avoiding dichotomization. Additivity will be addressed with interaction terms. The proportional hazards assumption will be tested using Schoenfeld residuals. We will use mixed models to analyze the impact of ventilatory variables collected during hospitalization on the main clinical outcomes. We will perform complete case analyses, without missing data. We will also perform a sensitivity analysis using multiple imputation.

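### Screening extra variables at univariate p<0.20 with significance-guided entry is likely to report some null variables as independent risk factors, and the claim of a sufficient sample has no stated event or parameter basis

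*Protocol article*

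**What the plan says.** The Statistical analysis plan section of the protocol article sets out one modelling route on one data set.

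- **Candidates.** The Table 5 variables are named a priori and face no screen. Additional variables with p below 0.20 "in a univariate analysis will be evaluated as independent risk factors of poor prognosis in a multivariable Cox model".
- **Entry.** "The order of inclusion of variables into Cox multivariable models will follow statistical significance criteria and clinical relevance". No entry threshold is given.
- **Final model.** Alternatives are compared by information criteria and likelihood-ratio tests. Splines or polynomials and interaction terms can add parameters.
- **Testing.** "All hypothesis tests will be two-tailed, with a significance level of 0.05".
- **Aim.** The Cox model is used "to identify the main risk factors for ICU survival beyond expected associations, such as age, comorbidity burden, and severity of disease at ICU admission".

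On size, the section says "A sample size of 300 patients was initially anticipated". It then says "we revised the anticipated sample size to 500 patients", a change it links to new ICU beds. Finally it plans to take every patient in the period, "a sample possibly larger than the anticipated sample size". It concludes: "Such a large sample would suffice to allow identification of predictors of survival". The main analysis is complete-case, with multiple imputation as a sensitivity analysis.

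**The concern.** The screen, the order of entry and the choice between models all look at the same outcome data. Variables survive partly because chance made their estimates large, and ordinary Cox p-values and intervals take no account of that. A univariate p<0.20 rule gives little protection: every variable that would reach 0.05 on its own has already passed it. The pool it draws from is open, while the parameter count also grows through splines and interactions.

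At stake is the list of risk factors for mortality that the Discussion promises for the main manuscript and plans to compare with the literature. The descriptive results and the Kaplan-Meier estimates are not affected.

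**Working it through.** **The plan's own figure.** Neither 300 nor 500 comes with an effect size, power, event rate or candidate count, so neither can be reproduced. One guess happens to fit: 20 rows in Table 5 x 10 deaths each = 200 deaths, and 200 / 0.40 = 500. The article does not state that basis, and the same guess gives 572 at 35% mortality and 445 at 45%.

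**Inputs**
- Table 5 has 20 rows but 19 distinct variables, because pH is listed twice. On my reading 15 are continuous and 4 binary.
- Additional pool (not stated, so an assumption counted from the table shells): 31 variables in Tables 1 and 2 that are not in Table 5, or 57 with the all-patient items of Table 3.
- Mortality: 28-day ICU mortality is not given. The proxy is 35% to 45%, the Discussion's benchmark for hospital mortality in ventilated patients.
- Splines: 2 to 3 df per continuous variable (assumed).

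**Deaths per parameter at N=500.** Deaths = 500 x 0.35 = 175 to 500 x 0.45 = 225.

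| Model | df | Deaths per parameter |
|---|---|---|
| Table 5, linear | 19 | 9.2 to 11.8 |
| Table 5, 2-df splines | 15 x 2 + 4 = 34 | 5.1 to 6.6 |
| Table 5, 3-df splines | 15 x 3 + 4 = 49 | 3.6 to 4.6 |
| Table 5 + 31 extras, linear | 50 | 3.5 to 4.5 |
| Table 5 + 57 extras, linear | 76 | 2.3 to 3.0 |

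Interactions are not counted, and complete-case analysis lowers every figure by an unknown amount.

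**Chance findings by arithmetic (independent null extras)**
- Expected to pass p<0.20: 31 x 0.20 = 6.2, or 57 x 0.20 = 11.4.
- Expected at p<0.05: 31 x 0.05 = 1.6, or 57 x 0.05 = 2.9.
- At least one at p<0.05: 1 - 0.95^31 = 0.80, or 1 - 0.95^57 = 0.95.

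**Simulation.** There were 200 runs per setting with 40% deaths. The 19 a priori variables (6 with true effects, 13 null) were exempt from the screen. The 31 or 57 null extras were either independent of these or weakly correlated with them. Extras were screened at p<0.20, followed by forward entry at 0.05.

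| Result | N=500 (200 deaths) | N=1,500 (600 deaths) |
|---|---|---|
| At least one null extra reported | 59% to 95% | 74% to 88% |
| Share of retained variables that are null | 25% to 42% | 24% to 33% |
| Coverage of nominal 95% intervals, retained variables | 53% to 70% | 63% to 73% |

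At N=500 the mean number of null extras reported was 0.85 to 1.43 with 31 extras and 1.74 to 2.77 with 57. Entry at the AIC-equivalent 0.157 gave coverage of 66% to 77%.

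**Comparators at N=500.** A fixed Table 5 model without selection had coverage of 93% to 94%, and about 15% of its findings at p<0.05 were null variables. With Table 5 forced in and no selection after the screen, coverage for the screened extras was 76% to 77% if independent and 95% to 96% if correlated. Most of the loss therefore comes from selection after the screen.

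**The case against.** Several counter-arguments have force.

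- **A condensed article may leave shrinkage and validation to a fuller plan.** That stands, and their absence is not the point. The point is the selection rule that the article does state.
- **Table 5 bypasses the screen, and clinical relevance also guides entry.** Both are true. The simulation exempts Table 5 but cannot model clinical judgement, which might remove some null variables. So the route is likely, not certain, to mislabel.
- **The candidate pool is assumed.** Nothing says that every row of Tables 1 to 3 will be screened, and items such as ferritin or diabetes may have real effects. The ranges are illustrations.
- **The cohort may be well above 500.** Bed numbers in Study design and location suggest about 45 x 250 + 30 x 300 = 20,250 bed-days from mid-April to the end of June. At assumed stays of 10 to 20 days and 70% to 90% occupancy, that is roughly 700 to 1,800 admissions. With 1,500 patients (525 to 675 deaths), Table 5 with splines would have 10.7 to 19.9 deaths per parameter. This answers much of the parameter-count worry, but not the selection problem.

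A reader might also infer two stronger points that the article does not support. One is that U-shaped predictors will be lost at the screen: no sentence says the screen fits linear terms only. The other is that age, comorbidity and severity may be dropped: all are in Table 5, and the stated aim implies adjusting for them. Their retention is simply not made explicit.

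**Conclusion.** The concern holds as a flaw in a stated rule. Followed as written, the p<0.20 screen with significance-guided entry and data-driven model choice is likely to report some null variables as independent risk factors, with intervals below nominal coverage. The simulated sizes depend on the assumed pool of extras, 40% deaths, the entry threshold and illustrative effects and correlations. The direction does not depend on the cohort being small, since under-coverage persists at 1,500 patients.

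On sample size the conclusion is weaker. A reader might infer that the sample is shown to be too small. The article does not support that, because the final number, the ICU mortality and the candidate count are all open. What can be said is that sufficiency is asserted without a basis. At 500 patients it is doubtful for Table 5 with splines or for an open pool, and borderline for Table 5 as linear terms.

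**What to change.** - Drop the p<0.20 screen and significance-ordered entry from the main model.
- Fit one prespecified Cox model of the Table 5 variables. Enter pH once, and settle in advance the overlap between SAPS 3 or SOFA and their component variables. State that age, Charlson score and severity are always retained.
- Fix the total df in advance from expected deaths, not observed ones. At 10 deaths per parameter (a rule of thumb, assumed here), 175 to 225 deaths support about 17 to 22 parameters. The 19 linear terms nearly fill that, so splines should go to a short prespecified list that fits the budget.
- Report any additional variables separately as exploratory, with shrinkage or a bootstrap that repeats the whole selection.
- Replace the sufficiency sentence with the expected number of deaths and the number of parameters they support.

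This changes the analysis wording only, with no change to data collection. The cost is a shorter main table, with other associations labelled exploratory.

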## DISCUSSION

Our study will report characteristics and outcomes of all patients admitted to the ICU at the largest academic hospital in Brazil during the peak of the pandemic of COVID-19 in Sao Paulo. The hospital developed a preparedness plan that included grouping COVID-19 patients in a building dedicated exclusively for the care of these patients, creation of surge ICUs to increase ICU bed capacity, and hiring additional healthcare professionals to work exclusively in the COVID-19 ICUs. The actions were coordinated by a crisis committee composed of critical care specialists, pulmonologists, infectious disease specialists, nurses, respiratory specialists, pharmacists, engineers, and administrators, among others, who met daily to make shared decisions. Such an effort helped prevent shortage of personal protective equipment and important medications, facilitated the development of institutional protocols for patient care and infection control, and contributed to a rational distribution of limited resources with potential impact on patient outcomes (28). The results will allow for the assessment of clinical outcomes of critically ill patients that will be representative of a middle-income country in a highly strained environment caused by the pandemic. Overall healthcare inequity in the treatment of chronic comorbidities in the Brazilian healthcare system, delayed access to proper critical care, and heterogeneity in ICU within the hospital (surge *vs.* previously functioning ICUs) are some of the system-level characteristics that highlight the importance of this study to assess overall survival of COVID-19 patients in LMICs.

We will also be able to assess resource utilization beyond mechanical ventilation, such as renal replacement therapy and ICU length of stay, to characterize the burden of this surge of severe respiratory failure patients to our hospital and healthcare system. In the main manuscript, both characterization of the cohort and the risk factors for increased mortality will be assessed and compared to the current literature. Our main benchmark for ICU and hospital survival is the result published regularly by the Intensive Care National Audit & Research Centre (ICNARC), that is, 35%-45% hospital mortality among patients receiving mechanical ventilation (29), which represents the outcomes of a universal healthcare system in a HIC.

In addition, the study will provide answers to many ancillary research questions:

Rate of use and success rate of non-invasive ventilation and high-flow nasal cannula use to treat respiratory failure and of commonly used strategies for refractory respiratory failure, including inhaled nitric oxide, prone positioning, and ECMO.Prediction models of hospital mortality specific for COVID-19.Characterization of subgroups of interest, such as oncologic and transplant patients.System-level research questions to compare outcomes and processes of care in “surge” ICUs and previously functioning ICUs, which would allow planning for future surges in critical care capacity.

In conclusion, we will be able to describe the characteristics and outcomes of a large sample of critically ill patients with COVID-19 admitted to a dedicated hospital in a LMIC, which could inform health policy and resource allocation and allow for many exploratory research questions to be answered.

## Figures and Tables

**Figure 1 f01:**
[figure not shown]
Expected flow of potentially eligible participants in the study.

**Figure 2 f02:**
[figure not shown]
Overview of data collection and follow up in the study.

**Table 1 t01:** Baseline characteristics at ICU admission.

Variable	All participants (n)
Age, years	mean (SD)
Race*	
White	No. (%)
Black	No. (%)
Brown	No. (%)
Asian	No. (%)
Indigenous	No. (%)
Other - not declared	No. (%)
Male sex	No. (%)
Body-mass index (kg/m^2^)	mean (SD)
SAPS 3	mean (SD)
SOFA	median (IQR)
Charlson’s comorbidities score	median (IQR)
Comorbidities	No. (%)
Asthma	No. (%)
Chronic Obstructive pulmonary disease	No. (%)
Cardiovascular disease	No. (%)
Hypertension	No. (%)
Diabetes	No. (%)
Chronic kidney disease of any stage	No. (%)
Cancer	No. (%)
Other	No. (%)
Symptoms	No. (%)
Loss of smell or taste	No. (%)
Fatigue	No. (%)
Headache	No. (%)
Altered level of consciousness	No. (%)
Rhinorrhea	No. (%)
Diarrhea	No. (%)
Shortness of breath	No. (%)
Sore throat	No. (%)
Fever	No. (%)
Myalgia	No. (%)
Cough	No. (%)
Duration of symptoms before admission, days	median (IQR)
Treatment before ICU admission	No (%)
Chloroquine or hydroxychloroquine	No (%)
Systemic corticosteroids	No (%)
Azithromycin	No (%)
Other antibiotics	No (%)

SAPS 3: Simplified acute physiology score; SOFA: Sequential Organ Failure Assessment score; *The categories represent the Brazilian official race classification.

**Table 2 t02:** Laboratory findings at ICU admission.

Variable	patients (n)
Arterial lactate mg/dL	mean (SD)
Aspartate aminotransferase - U/L	mean (SD)
Alanine aminotransferase - U/L	mean (SD)
Total bilirubin - mg/dL	mean (SD)
Creatinine - mg/dL	mean (SD)
Creatine kinase - U/L	mean (SD)
D-dimer - ng/mL	mean (SD)
Lactate dehydrogenase - U/L	mean (SD)
Ferritin - ng/mL	mean (SD)
White blood cell count/mm^3^	mean (SD)
Lymphocyte count/mm^3^	mean (SD)
Platelet count/mm^3^	mean (SD)
C-reactive protein - mg/L	mean (SD)

**Table 3 t03:** Patient management on day 1 after ICU admission.

Variables	All patients (n)
Sedation	No. (%)
Midazolam	No. (%)
Propofol	No. (%)
Fentanyl	No. (%)
Dexmedetomidine	No. (%)
Other	No. (%)
Respiratory support	
Oxygen catheter or mask	No. (%)
High-flow nasal cannula	No. (%)
Non-invasive ventilation	No. (%)
Invasive mechanical ventilation	No. (%)
Parameters during invasive ventilation (n=XXX)	
Tidal volume (mL)	mean (SD)
Minute volume (L/min)	mean (SD)
FIO_2_ (%)	mean (SD)
PaO_2_/FIO_2_	mean (SD)
PEEP (cmH_2_O)	mean (SD)
Plateau pressure (cmH_2_O)	mean (SD)
Driving pressure (cmH_2_O))	mean (SD)
pH	
PaCO_2_ (mmHg)	mean (SD)
Oxygen saturation (%)	mean (SD)
Rescue therapies	No. (%)
Prone position	No. (%)
Neuromuscular blockade	No. (%)
Inhaled pulmonary vasodilators	No. (%)
Extracorporeal membrane oxygenation	No. (%)
Recruitment maneuvers	No. (%)
PEEP titration by compliance or driving pressure	No. (%)
Vasopressors	No. (%)
Antibiotics	No. (%)
COVID-19 specific treatment	No. (%)
Chloroquine or hydroxychloroquine	No. (%)
Dexamethasone	No. (%)
Methylprednisolone	No. (%)
Hydrocortisone	No. (%)
Prednisone	No. (%)
Azithromycin	No. (%)
Lopinavir / ritonavir	No. (%)
Tocilizumab	No. (%)
Anticoagulation, No. (%)	No. (%)
Prophylactic dose	No. (%)
Full anticoagulation	No. (%)
Limitation of treatment	No. (%)

FIO_2_: fraction of inspired oxygen; PaO_2_: arterial partial pressure of oxygen; PEEP: positive pressure at end expiration.

**Table 4 t04:** Clinical outcomes at ICU discharge.

Variable	Patients
Resource utilization	
Invasive mechanical ventilation	No. (%)
Prone positioning	No. (%)
Duration of Mechanical ventilation (days)	Median (IQR)
Use of NIV*	No. (%)
Use of high-flow nasal cannula*	No. (%)
Need for vasopressors	No. (%)
Renal replacement therapy	No. (%)
Tracheostomy	No. (%)
Clinical complications during ICU stay	
Delirium	No. (%)
Thrombotic phenomena	No. (%)
Ventilator-associated pneumonia	No. (%)
Cardiac arrythmias	No. (%)
Clinical outcomes	
ICU length of stay (days)	Median (IQR)
Hospital length of stay (days)	Median (IQR)
ICU mortality	No. (%)
Hospital mortality	No. (%)

*To avoid intubation or before intubation.

**Table 5 t05:** Predictors of ICU survival at 28 days.

Variable	Survivors (n)	Non-survivors (n)	*p*-value*
Baseline characteristics			
Age,	mean (SD)	mean (SD)	
Male sex	No. (%)	No. (%)	
Charlson’s comorbidity score	Median (IQR)	Median (IQR)	
Obesity	No. (%)	No. (%)	
Acuity variables at admission#			
Need for vasopressors	No. (%)	No. (%)	
Invasive mechanical ventilation	No. (%)	No. (%)	
Glasgow coma scale	Median (IQR)	Median (IQR)	
Creatinine (mg/dL)	mean (SD)	mean (SD)	
Platelets	mean (SD)	mean (SD)	
Bilirubin (mg/dL)	mean (SD)	mean (SD)	
pH	mean (SD)	mean (SD)	
SAPS 3	mean (SD)	mean (SD)	
SOFA day 1	Median (IQR)	Median (IQR)	
Disease characteristics			
Time from symptom onset to ICU admission	Median (IQR)	Median (IQR)	
Number of days of intubation before ICU admission	Median (IQR)	Median (IQR)	
Other laboratorial results			
D-dimer (ng/mL)	mean (SD)	mean (SD)	
Lactate dehydrogenase (U/L)	mean (SD)	mean (SD)	
Lymphocyte count (cells/mm^3^)	mean (SD)	mean (SD)	
Arterial lactate (mg/dL)	mean (SD)	mean (SD)	
pH	mean (SD)	mean (SD)	

**p*-value will come from univariate Cox proportional hazards model.

^#^During the first 24h of ICU stay.

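### Days of intubation before ICU admission is an a priori predictor with no denominator and no companion yes/no term, so its effect cannot be separated from that of arriving intubated

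*Protocol article*

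**What the plan says.** Table 5, on predictors of 28-day ICU survival, has columns for survivors and non-survivors. Under disease characteristics it has the row "Number of days of intubation before ICU admission", summarised by median and IQR. Its footnote says that the p-value "will come from univariate Cox proportional hazards model". No row records whether the patient was intubated before ICU admission. The nearest is invasive mechanical ventilation, one of the acuity variables that a second footnote places in the first 24 hours of the ICU stay.

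The Statistical analysis plan section uses Table 5 as its list of variables chosen in advance ("as clinically relevant (Table 5) and additional variables with a" p-value below 0.20). These "will be evaluated as independent risk factors of poor prognosis in a multivariable Cox model". The order of inclusion follows significance and clinical relevance, and alternative models are compared by information criteria and likelihood-ratio tests. On missing values: "We will perform complete case analyses, without missing data", with multiple imputation as a sensitivity analysis.

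The Study population section admits consecutive adult ICU patients whether or not they are ventilated. Table 3, by contrast, gives its ventilator parameters a denominator of their own.

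**The concern.** Days of intubation before ICU admission describes how long only for patients who arrived intubated. For everyone else it is either 0 or not applicable, and the article does not say which. The choice decides what the coefficient means.

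Coded 0, the step from 0 to 1 day carries everything that distinguishes patients who arrive intubated from the rest, and a per-day hazard ratio absorbs it. The first-24-hour ventilation row does not prevent this, because it pools patients who arrived intubated with those intubated in the ICU on day 1. The Table 5 medians would also be 0 in both columns whenever fewer than half of each group arrived intubated.

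Coded missing, a complete-case model that contains the term is a model of patients who arrived intubated, not of the cohort.

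At stake is one of the study's stated aims, the identification of risk factors. Length of pre-ICU intubation could be reported as an independent risk factor, or as protective, when the data show only that patients who arrive intubated differ.

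**Working it through.** The plan has no figure of its own to reproduce. The 500 patients are an anticipated number, with no effect size, event count or power.

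**Inputs from the article.** 500 patients; two-sided 0.05; censoring at 28 days; first-24-hour ventilation in the same candidate list.

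**Inputs assumed, because the article gives none.** The share arriving intubated, the hazard ratios and the distribution of pre-ICU days.

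**If coded 0.** Cox models were simulated with the true effect of duration set to zero. The hazard was 0.010 per day × (ventilation HR if ventilated in the first 24 hours) × (extra HR if arriving intubated). Baseline 28-day mortality is therefore 1 − exp(−0.28) = 24%. Either 40% arrive intubated and 25% are intubated in the ICU, or 20% and 40%. There were 150 datasets per setting, so the Monte Carlo standard error is √(0.05 × 0.95/150) = 1.8 points near 5% and √(0.4 × 0.6/150) = 4.0 points near 40%. The table shows how often days reached p < 0.05 at n = 500.

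| Arriving intubated | Ventilation HR | Extra HR for arriving intubated | Days, adjusted for first-24-hour ventilation | Indicator added as well | Only those arriving intubated |
|---|---|---|---|---|---|
| 40% | 2 | 1 | 7.3% | 4.7% | 5.3% |
| 20% | 2 | 1 | 8.0% | 6.7% | 6.0% |
| 40% | 2 | 1.5 | 32.7% | 4.7% | 4.7% |
| 20% | 2 | 1.5 | 44.0% | 4.7% | 5.3% |

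Across all settings with no extra risk for arriving intubated (ventilation HR 1 to 3), the rate adjusted for ventilation was 3% to 9%.

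A second simulation used 35% not ventilated, 35% intubated in the ICU (HR 2.0-2.5) and 30% arriving intubated (HR 1.3, 1.7 or 3.0), with 300 datasets per setting. Where the two ventilated groups differed in hazard, days adjusted for first-24-hour ventilation was significant in 29-44% of datasets at n = 500. The hazard ratio per day was about 0.94-0.95 when those arriving intubated fared better than those intubated in the ICU, and about 1.04 when they fared worse. With equal hazards the rate was 6-7%. With the indicator added, or with restriction to patients who arrived intubated, it was 4-7%.

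**If coded missing.** The univariate test then uses only patients who arrived intubated and is valid for duration. A complete-case multivariable model containing the term keeps the same patients. At the assumed shares this is 0.20 × 500 = 100 or 0.40 × 500 = 200 patients, a loss of 400 or 300. Among them the first-24-hour ventilation row hardly varies, so its own effect could not be estimated. Multiple imputation does not repair this, because it would assign pre-ICU intubation days to patients who had none.

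**The case against.** The strongest reply is that Table 5 is an empty shell in a condensed article. A count of days before admission is naturally 0 for a patient who was not intubated, the coding of a derived covariate is often left to a fuller document, and Table 3 shows that the authors do use sub-denominators. It is true that the coding is not stated, so neither consequence is written in the plan, and the two cannot both occur. But the article itself fixes the predictor, its summary, its test and the missing-data rule, and neither coding gives a clean result under those choices.

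A reader might infer that the univariate p-value would be a false positive, since with zero coding it rejects often (53% at ventilation HR 2 with 40% arriving intubated). The documents do not support that. In those simulations arriving intubated goes with a truly higher hazard, so an unadjusted association is real. The difficulty lies in reading it as an effect of duration.

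A reader might also infer that every Table 5 row is forced into one model. The plan says only that the variables will be evaluated, so the complete-case loss arises only in models that contain this term.

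Two further points limit the size. SAPS 3, SOFA and other acuity rows could account for part of a hazard difference between the ventilated groups; the simulations did not include them. The plan also intends splines or polynomials, whereas the rates above come from a linear term. Flexibility does not help here: with a square-root term added in the second simulation, joint rejection rose to 52-69% at n = 500, because a curve fits the jump from 0 to 1 day more closely.

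**Conclusion.** The point holds in a limited form. The plan names a duration that is informative only for patients who arrive intubated as an a priori predictor for the whole cohort, without a denominator and without the indicator needed to interpret it. With zero coding, duration is separated from status only if both ventilated groups have the same hazard. If they differ as assumed above, a duration with no effect is significant in roughly 30-44% of datasets at n = 500, against about 5% with the indicator. If they do not differ, the multivariable result is near nominal. With missing coding, the harm is instead the loss from the model of everyone who did not arrive intubated. The percentages rest on assumed prevalences, hazard ratios and day distributions, and show what could happen rather than what will.

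A reader might go on to infer that the Table 4 row "Duration of Mechanical ventilation (days") understates ventilation for patients who arrive intubated. The article does not support this. It gives no time origin for ventilation days, and the row stands under resource utilization, where days ventilated in the ICU are a legitimate measure.

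The Kaplan-Meier estimates of the main outcome and the other descriptive aims are unaffected.

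**What to change.** Where this variable is evaluated in the Cox model, enter two terms together: intubated before ICU admission (yes/no), and days intubated before ICU admission (0 if no). The days coefficient then describes duration among those who arrived intubated, the indicator carries the difference in status, and no patient is lost for lack of a value.

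In Table 5, show the median, IQR and p-value for days only among patients who arrived intubated, and print their n, as Table 3 does for its ventilator parameters.

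The cost is one extra degree of freedom and one changed table row. The indicator is derived from data already collected. Table 4 needs no change on this account.
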